### Statistical Analysis

Primary analyses will be conducted using linear mixed-effects models to evaluate the impact of the intervention on both momentary and self-report outcomes. Time (T0, T1, T2, and T3) will be included as a within-subject factor, while intervention (intervention 1 vs intervention 2) and group (clinical vs subclinical) will be modeled as between-subject factors. Random intercepts for participants and random slopes for time will be specified. Secondary analyses will explore potential moderators and mediators of treatment response, including app engagement, baseline severity, and demographic variables. Missing data will be addressed using maximum likelihood estimation under the assumption that data are missing at random.

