### Screening, Baseline, and Follow-Up Assessments

Interested individuals are being contacted by the study’s research assistant and invited to attend a screening interview, during which they receive detailed information about the study, undergo an eligibility assessment for participation, and provide informed consent in electronic or paper form. For participants younger than 18 years, parental consent is also required. Upon consent, participants complete the online assessment protocol consisting of sociodemographic information and validated self-report questionnaires. Participants are invited to complete online questionnaires at multiple time points throughout the study to assess primary and secondary outcomes and momentary data during the app-based intervention. Figure 2 provides an overview of the instruments administered at each assessment point (T0-T3), including baseline, treatment start, postintervention, and 3-month follow-up evaluations.

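### T0 is modelled as an outcome level with no baseline adjustment or common-baseline constraint, so on the usual arm-by-time reading the effect on repeated self-report scales is an unadjusted change contrast: unbiased, but less precise than it could be

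*Protocol article*

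**What the plan says.** The Statistical Analysis section states one model family for the outcomes: "Primary analyses will be conducted using linear mixed-effects models to evaluate the impact of the intervention on both momentary and self-report outcomes". On the mean structure it says "Time (T0, T1, T2, and T3) will be included as a within-subject factor" and "intervention (intervention 1 vs intervention 2) and group (clinical vs subclinical) will be modeled as between-subject factors". On the covariance it says "Random intercepts for participants and random slopes for time will be specified". Baseline level is mentioned only here: "Secondary analyses will explore potential moderators and mediators of treatment response, including app engagement, baseline severity, and demographic variables". Missing values are handled as follows: "Missing data will be addressed using maximum likelihood estimation under the assumption that data are missing at random".

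T0 therefore sits in the outcome vector. The section does not write an arm-by-time term, does not name the contrast that measures the treatment effect, and does not say whether the arms may differ at T0.

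The Screening, Baseline, and Follow-Up Assessments section places the first questionnaires at consent: "Upon consent, participants complete the online assessment protocol consisting of sociodemographic information and validated self-report questionnaires". It gives T0 to T3 as baseline, start of treatment, end of intervention and 3-month follow-up. The Methods part of the abstract instead lists baseline, 6 weeks, 1 month and 3 months. The Primary Outcome section has the ISAS covering lifetime at T0 and the last month at follow-up.

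**The concern.** Randomization makes the expected arm difference at T0 zero. A model that has T0 as one more outcome level and leaves the arm difference there free estimates a quantity already known to be zero in expectation, then subtracts that estimate from the later difference. Baseline is subtracted with weight 1, whereas adjustment would use weight rho, so chance imbalance at T0 passes into the estimate more than it should.

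At stake is the width of the confidence intervals for emotion regulation, symptoms, social support and well-being, for those scales given in the same form at T0 and later. When rho is below 0.5, the change contrast is less precise than ignoring baseline altogether, because 2(1-rho) then exceeds 1. The Discussion concedes that the trial may lack power for small-to-moderate effects, which is where adjustment helps most.

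**Working it through.** **Inputs from the article.** T0 as a level of time, arm and group as between-subject factors, random intercept and slope (Statistical Analysis). f=0.27, 90% power, alpha .05, 100 per group, 20% attrition, 120 per arm (Sample Size Calculation).

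**Inputs assumed.** rho from 0.3 to 0.9; equal SDs at T0 and follow-up; complete data; one later visit compared with T0. The documents give no correlation and no SD.

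**The plan's own figure.** A noncentral F test with four cells (arm by clinical/subclinical group), 3 numerator df and f=0.27 reaches 90% power at N=199, with power 0.903 at N=200. That reproduces 100 per arm. A two-arm comparison at the same f (d = 2 × 0.27 = 0.54) needs N=147 and has power 0.967 at N=200. Neither calculation uses a baseline measurement. After 20% attrition, 120 × 0.8 = 96 per arm remain.

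**Variance of the two estimators.** With n per arm and common SD σ:

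- change contrast: (2σ²/n) × 2(1-rho)
- baseline-adjusted or constrained-baseline: (2σ²/n) × (1-rho²)

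The ratio of adjusted to change is (1-rho²)/[2(1-rho)] = (1+rho)/2, so the loss is 1-(1+rho)/2 = (1-rho)/2.

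| rho | 2(1-rho) | 1-rho² | Information lost | SE larger by | 240 worth, under adjustment |
|---|---|---|---|---|---|
| 0.3 | 1.40 | 0.91 | 35% | 24% | 156 |
| 0.5 | 1.00 | 0.75 | 25% | 15.5% | 180 |
| 0.7 | 0.60 | 0.51 | 15% | 8.5% | 204 |
| 0.8 | 0.40 | 0.36 | 10% | 5.4% | 216 |
| 0.9 | 0.20 | 0.19 | 5% | 2.6% | 228 |

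**Sensitivity to the assumptions.** Each triple is for rho 0.3, 0.5 and 0.7.

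- Four-visit generalized least squares, random intercept only: exactly 35%, 25%, 15%.
- Adding a random slope (assumed slope variance 0.02 to 0.05, T0 variance 1): 27-35%, 17-25%, 9-15%, depending on visit.
- Time as a linear slope: 29-40%, 18-27%, 8-15%.
- Follow-up SD 1.2 times baseline: 24%, 13%, 3%. At 0.8 times: 50%, 43%, 37%.
- Mean of three follow-ups minus T0: 53%, 38%, 23%.

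**Power.** Noncentral F, 1 df, N=192, noncentrality 48 × d²/v, where v is 2(1-rho) or 1-rho².

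| d | rho | Change contrast | Adjusted |
|---|---|---|---|
| 0.40 (assumed) | 0.3 | 64% | 82% |
| 0.40 (assumed) | 0.5 | 79% | 89% |
| 0.40 (assumed) | 0.7 | 95% | 97% |
| 0.54 | 0.5 | 96% | 99% |

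**The other literal reading.** If only an arm main effect were tested, the T0 difference, zero in expectation, would be averaged in. With four balanced, equally weighted visits, a constant effect at T1 to T3 shrinks to 3/4 of its size. If T1 is also before treatment, it shrinks to 2/4.

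**The case against.** The strongest reply is that the criticised model is inferred. The section writes no interaction and no contrast, and a constrained-baseline mixed model also has T0 as a level of time, so the text does not exclude it. Exact fixed effects are often left to an analysis plan, which is not shown. This stands in part, and the point must be worded conditionally. It does not remove the point. The article does assign T0 a role, as an outcome level, and gives baseline severity a place only in secondary analyses. The hypothesis of a larger reduction under the specific app fits an arm-by-time contrast, and the main-effect reading is worse.

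Three further objections stand as limits:

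- The schedule by instrument is in a figure that is not available, so which scales are repeated in the same form at T0 and later cannot be listed with certainty.
- At the effect size nearest the plan's own (d=0.54), the gain at rho 0.5 is about 3 points; the larger gains use d=0.4, which is not in the documents.
- The sample size takes no credit for baseline adjustment, so no stated power claim fails.

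A reader might infer that the planned analysis is biased or inflates type I error. On the arm-by-time reading it does not; that analysis is valid and common. A reader might also take 15% to 35% as an established loss. It rests on an assumed rho and equal SDs, and other plausible inputs run from almost nothing to over 50%. Nor does the point reach the primary ISAS frequency, where T0 and follow-up do not measure the same quantity.

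**Conclusion.** The point holds as a free improvement in efficiency, not as an error that invalidates the analysis. As written, T0 is an outcome level and no adjustment or constraint is stated. If the treatment effect is the arm-by-time contrast with a free T0 difference, about (1-rho)/2 of the attainable information is lost: 15% to 35% for rho 0.7 to 0.3, and 5% to 10% for rho 0.9 to 0.8, given equal SDs. The planned random slope lowers the figure somewhat, and unequal SDs can move it either way. The conclusion is confined to self-report scales given in the same form at T0 and later, which are secondary outcomes.

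**What to change.** First reconcile the two definitions of T0 to T3 (abstract Methods against Screening, Baseline, and Follow-Up Assessments) and say whether T1 is measured before app access.

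Then add one sentence to the Statistical Analysis section. For each self-report scale given in the same form at T0 and later, constrain the arm means to be equal at T0 within the clinical and subclinical groups: no intervention effect and no intervention-by-group effect at T0, with intervention-by-time kept for the post-treatment visits. Alternatively, take only post-treatment visits as outcomes, with the T0 score and T0-by-time as covariates. Name that post-treatment contrast as the treatment effect. If T1 precedes app access, treat it as pre-treatment too. Do not apply this to the ISAS frequency.

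The cost is one sentence, with the same data and software and no extra participants. The constrained form keeps participants with partial data under the stated maximum likelihood approach. Its one added assumption, equal expected T0 means, follows from randomization provided T0 is completed before app access. Recruitment stood at 145 of 240 in January 2026, and the article dated completion of the analysis to October 2026, so the model should be fixed before the outcome data are analysed by arm.

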### Ethical Considerations

The study received ethics approval from the Research Ethics Committee of Bellvitge University Hospital on December 12, 2022 (reference PR336/22; CSA PR4/2022). All prospective participants are provided with written information clarifying that their involvement in the study is entirely voluntary. They are informed that choosing not to participate will not result in any negative consequences and that they retain the right to withdraw from the study at any point without penalty. Additionally, participants are given the opportunity to seek clarification or ask any further questions.

Participant privacy and confidentiality are strictly protected. Personal data are pseudonymized and stored on secure, encrypted servers, accessible only to authorized members of the research team. Data handling procedures comply with applicable data protection regulations, including the General Data Protection Regulation (EU 2016/679). No personally identifiable information will be included in study analyses or publications. Participants who complete the full intervention receive financial compensation of €45 (US $52.20). Compensation is provided for time and resources invested and is not contingent on study outcomes.

For ethical reasons, when the group assigned to intervention 2 completes the posttreatment assessment (2 months after the baseline evaluation), the Kalmer app will be offered to participants in the control group if the study shows a significant reduction in the frequency of NSSI.

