**Objective:**

This randomized controlled trial will evaluate the effectiveness of Kalmer, a brief app-based intervention for reducing NSSI and improving emotional well-being. The study has 2 aims: (1) to evaluate a newly developed app-based intervention for adolescents and young adults engaging in NSSI and (2) to assess predictors of treatment outcomes for this app-based intervention. We hypothesize that participants receiving a mobile app–based brief intervention specifically tailored to address NSSI will show a greater reduction in NSSI frequency at the end of treatment and at follow-up than participants receiving a nonspecific app-based intervention. In this paper, we present our study protocol.

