**Methods:**

This 2-arm randomized controlled trial, lasting 6 weeks, will include 240 participants aged 14 to 24 years who engage in NSSI. The intervention app, Kalmer, was developed through iterative consultation with clinical and research experts and guided by survey results and evidence-based frameworks such as dialectical behavior therapy and cognitive behavioral therapy. The intervention will include 5 core components: distress tolerance, emotion regulation, mindfulness and self-compassion, interpersonal regulation, and problem-focused coping. The app will deliver multimedia-based ecological momentary interventions triggered by real-time ecological momentary assessments to tailor support to users’ current contexts and needs. Participants are randomized to receive either the Kalmer intervention or a psychoeducational control app. The primary outcome will be NSSI frequency, assessed through self-report at baseline, 6 weeks after intervention, and at 1-month and 3-month follow-ups.

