#### Primary Outcome

The primary outcome is the frequency of NSSI behaviors, assessed using the ISAS [24] at the predefined study time points. At baseline (T0), the ISAS assesses the lifetime frequency and functions of NSSI behaviors [24]. At follow-up assessments, a modified version of ISAS is used to inquire about NSSI behavior in the last month. The Spanish version of the ISAS is used in this study, demonstrating strong internal consistency for both the interpersonal and intrapersonal subscales (Cronbach α=0.87 and 0.90, respectively) [35].

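### The conditional offer of Kalmer to controls at posttreatment conflicts with the planned follow-up comparison and calls for an efficacy result before follow-up is complete

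*Protocol article*

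**What the plan says.** Ethical Considerations sets a time and a condition for offering the active app to the control arm. The time is "when the group assigned to intervention 2 completes the posttreatment assessment (2 months after the baseline evaluation"). The condition is that "the Kalmer app will be offered to participants in the control group if the study shows a significant reduction in the frequency of NSSI". No contrast, time point, significance level or data cut is attached to the condition.

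Elsewhere the article relies on between-arm data collected after that point:

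- **Abstract, Objective:** the hypothesis is that Kalmer participants "will show a greater reduction in NSSI frequency at the end of treatment and at follow-up" compared with controls.
- **Abstract, Methods:** the primary outcome is "assessed through self-report at baseline, 6 weeks after intervention, and at 1-month and 3-month follow-ups".
- **Screening, Baseline, and Follow-Up Assessments:** the T0-T3 schedule is described as "including baseline, treatment start, postintervention, and 3-month follow-up evaluations". The 3-month visit is there; the 1-month visit is not.
- **Statistical Analysis:** "Time (T0, T1, T2, and T3) will be included as a within-subject factor", so control data collected after an offer would enter the primary model.

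Three further statements bear on the point. Study Design calls the trial double-blinded. Randomization and Procedure gives 6 weeks of app access. Primary Outcome says that at follow-up "a modified version of ISAS is used to inquire about NSSI behavior in the last month", whereas the baseline version covers lifetime frequency.

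**The concern.** If controls can use Kalmer between posttreatment and their last follow-up, the follow-up contrast is no longer Kalmer against the control app. It becomes Kalmer against a mixture, and a lasting benefit is diluted towards no difference. The condition is likeliest to be met when Kalmer works, so the dilution would occur when there is a durable effect to detect.

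The condition also requires someone to know whether NSSI has fallen significantly while some participants are still being followed. A control who is then offered Kalmer can infer having been on the other version, and goes on to self-report the primary outcome.

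At stake are the follow-up half of the hypothesis and the later time points of the primary model. Exposure of controls cannot be undone afterwards.

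**Working it through.** **1. Timing.** The offer comes at posttreatment; the 3-month visit comes later on any schedule in the article. If follow-up is counted from posttreatment, 6 weeks of access starting there covers the whole last-month window of a 1-month visit. It ends before the last-month window of a 3-month visit, where the effect would be carry-over. If access starts later, or if 3 months is counted from baseline, the 3-month window overlaps directly. The article does not state the origin.

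**2. Two readings of the trigger time.**

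- *Each control on finishing posttreatment.* The 2-months-after-baseline clock is a participant's clock and favours this reading. Every control could be exposed before follow-up.
- *The whole arm having finished.* Early enrollees have completed follow-up and late enrollees have not. A rough share is those not yet enrolled in January 2026: (240 − 145)/240 = 39.6%, about 40%.

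Under both readings an efficacy result is needed before the 3-month data are complete.

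**3. What would count as a reduction.** The text names no contrast. A between-arm contrast at posttreatment compares like with like. A pre-post change does not, because the ISAS window moves from lifetime at T0 to the last month afterwards, and counts can fall for that reason alone.

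**4. The plan's own sample size.** Inputs from Sample Size Calculation: f = 0.27, 90% power, alpha .05, 100 per group, 120 per arm after allowing for 20% attrition. Using the noncentral F with λ = N·f²:

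- four-cell omnibus test (numerator df 3): N = 199, power at 200 = 0.903, which reproduces the stated 200;
- two-arm contrast (numerator df 1): N = 147, power at 200 = 0.967, which does not.

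So d = 2f = 0.54 for arm against arm is an assumption of this check; the article does not establish it.

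**5. Dilution at follow-up.** Let c be the share of controls who take up Kalmer and gain its full effect. The article gives no uptake figure, so c is assumed. The diluted effect is d(1 − c), and power ≈ Φ(d(1 − c)/√(2/n) − 1.96). With n = 120 × 0.8 = 96 per arm, √(2/96) = 0.1443:

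| c | effect | z − 1.96 | power |
|---|---|---|---|
| 0 | 0.54 | 1.78 | 96% |
| 0.25 | 0.405 | 0.85 | 80% |
| 0.50 | 0.27 | −0.09 | 46% |
| 0.75 | 0.135 | −1.02 | 15% |

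At 100 per arm the corresponding values are 97%, 82%, 48% and 16%. For the whole-arm reading, with all late controls taking it up, the effect is 0.54 × (1 − 0.396) = 0.326. At 100 per arm, 0.326/0.1414 − 1.96 = 0.35, so power is about 64%.

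**6. Type I error, under one condition only.** If the same hypothesis is tested once mid-trial and again at the end, each at two-sided .05 without adjustment, and either result may be claimed as success, simulation gives an overall error of 8.3% for a look at half the information and 7.9% at 145/240.

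**The case against.** The strongest defence is that this is a loosely worded post-trial offer. The phrase about what the study shows suggests a study-level result, and the article describes no interim analysis. The Results section expects recruitment to end by March 2026 and final results in October 2026. Adding 2 months to posttreatment (May) and 3 months of follow-up (August), the last visit would precede the final analysis. The full protocol and SAP are not shown and may say more. This explanation is plausible, but it does not fit a clause that sets the offer at the posttreatment assessment. A fuller plan could allocate alpha, yet that would not undo exposure timed before follow-up. What stands is that an unplanned interim test cannot be asserted as fact.

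Other limits also stand.

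- **The contrast.** A reader might infer that the trigger is a within-arm change that the recall window would satisfy by itself. The documents do not support that. No contrast is named, and the only stated hypothesis is between-arm, so the trigger is undefined and has not been shown to be wrong.
- **Type I error.** A reader might infer that the error rate is inflated outright. The stated use of the result is to offer an app; no stopping or efficacy claim is attached to it.
- **Size.** The power losses stack assumptions. d=0.54 is not established for the arm contrast, uptake has no source, and full effect in crossovers is a ceiling, since a control starting at posttreatment would be only part-way through the 6 weeks at 1 month.
- **The 1-month visit.** It appears in the abstract but not in the T0-T3 description in Methods, so the firm conflict is with the 3-month visit.

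**Conclusion.** The conflict is real and should be resolved before any control is offered the app. It lies in a stated rule, not in missing detail: a significance-dependent offer is timed at posttreatment, while the hypothesis, the outcome schedule and the primary T0-T3 model depend on later between-arm data. Depending on the reading, all controls or the late enrollees could be exposed during follow-up, an efficacy result is needed before the 3-month data are complete, and blinding is weakened for controls who receive the offer. The end-of-treatment comparison is unaffected, because each control is offered the app only after that assessment.

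The size depends on uptake and on the condition being met. The figures in the working (power of 80%, 46% or 15% against 96% without crossover, or about 64% under the whole-arm reading) are illustrative upper bounds on the damage. The 8.3% error rate applies only if an unadjusted early look is also used to claim efficacy.

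**What to change.** Reconcile Ethical Considerations with the hypothesis, the abstract's outcome schedule, the T0-T3 description and Statistical Analysis. When controls gain access is for the sponsor and the ethics committee to settle. Statistically, either of two routes is coherent:

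1. **Trigger after lock.** Define the trigger as the final, locked between-arm analysis of NSSI frequency, and state that no efficacy test is run before lock.
2. **Earlier access kept.** Declare posttreatment the only confirmatory between-arm comparison, record each control's access date, exclude control data after access from the between-arm follow-up estimate, and report that estimate as descriptive.

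Under either route, name the contrast as between-arm, so that the change of ISAS window cannot decide the matter. In the same edit, state whether a 1-month visit exists, from what date follow-up is counted, and how the abstract's 6 weeks relates to the 2 months after baseline.

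The cost is a short amendment, which must be consistent with what the 145 participants enrolled by January 2026 were told about access. The first route means a later offer to controls; the second gives up a confirmatory follow-up comparison.

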## Results

This study was funded in 2022 and received ethics approval in December 2022. It was also registered in the UK’s clinical study registry (International Standard Randomized Controlled Trial Number; ISRCTN63093907) in March 2025. As of January 2026, a total of 145 participants have consented to participate in our study and completed baseline assessments. Preliminary data show high app engagement and acceptability and positive user feedback regarding app usability and content. Recruitment is ongoing. We expected to complete recruitment by March 2026 and finish data analysis and publish final results in October 2026. We plan to publish the data and summary findings in a peer-reviewed journal and at conferences.

We anticipate that the results of this study will offer valuable insight into the prevalence and patterns of NSSI in both clinical and nonclinical populations, particularly in the postpandemic context. Using EMAs and self-report measures, we expect to detect real-time fluctuations in emotional states, social experiences, and NSSI urges and behaviors.

The Kalmer app–based intervention, delivered via EMIs tailored to real-time affective states, is expected to reduce the frequency and intensity of NSSI urges and behaviors. Improvements in ER, perceived social support, and self-compassion are also anticipated. Furthermore, we expect the intervention to show high acceptability and usability among young adults with a history of NSSI, as assessed through validated self-report scales.

